### Study treatment

The study involves the use of two medical foods (MF1 and MF2 - Kolfarma s.r.l.) containing ALAC, inulin, FOS, with the addition of NaB in a CDD patient population. Both products are indicated for pediatric age (> 3 years). The product must be taken orally and not parenterally.

MF1 is a dietary supplement aimed at improving intestinal dysbiosis containing ALAC (contains milk derivatives), FOS, inulin, sweetener (steviol glycosides from stevia), emulsifier (polysorbate 80).

The first-round supplementation will be administered for 12 weeks. One dose/day (2 g sachet) is intended to be administered orally once a day after dissolving in water.

MF2 is a special medical purpose food intended for the dietary treatment of drug-resistant epilepsy. It contains ALAC (contains milk derivatives), inulin, FOS, flavors, sucralose, polysorbate 80, and NaB.

The second-round supplementation will be administered for 12 weeks. For participants weighing <30 kg, a 4 g dose (i.e., one 4 g sachet) is intended to be administered orally once a day after dissolving in water, 15 min before meal. For participants weighing ≥30 kg, a 4 g dose (i.e., 4 g sachets) is intended to be administered orally twice a day (12 h interval) after dissolving in water, 15 min before meals.

Intake is not recommended in cases of proven hypersensitivity to one or more ingredients.

No known side effects are reported for the two products used in this study.

If a treatment tolerance problem should develop at any time during the study, the investigator may reduce the patient’s dose, with administration on alternate days. Patients unable to tolerate the treatment even after a dose interruption should be suspended from the study.

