### Participants

The study will enrol 20 CDD patients. The sample size for this study is dictated by the rarity of the condition, 1:40,000 live births (3), and considering that the number of CDD patients in Italy is about 60 (according to the report of the Patients Association “CDKL5 Insieme verso la cura”). The sample size is calculated based on the following assumptions: (1) the clinical success for an enrolled patient is defined as a reduction of at least 50% of the seizure frequency compared to baseline; (2) a clinically significant result is achieved if at least 35% of the enrolled patients reduce the seizure frequency by at least 50%.

With these premises, a McNemar exact test (“after vs. before”), applied to a sample of 20 subjects, reaches a power of 80%, less than an alpha-error of 5%, in verifying clinical success in 35% of cases, using the following inputs: percentage of positives that become negative = 0; percentage of negatives that become positive = 35.

Eligible patients from Italy who meet the defined inclusion and exclusion criteria will be recruited, after signing the informed consent.

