### Subject withdrawal

Patient parents/legal guardians may decide to terminate the study at any time.

The principal investigator, guarantor of the study, may decide to terminate a patient’s participation at any time if the enrolled subject presents adverse events or is not compliant with the study procedures, or after withdrawal of participation consent.

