### Statistical analyses

We will examine longitudinal changes, with particular emphasis on differences between baseline (T0) and post-MF1 (T1), as well as between the second baseline following washout (T2) and post-MF2 (T3).

In descriptive analyses, data will be presented as mean ±SD for continuous variables and as percentages for categorical variables. The primary endpoint will be measured using the McNemar exact test. Differences in continuous variables (scale scores, biomarkers) will be tested using the unpaired and paired t-test for independent and dependent samples, respectively, in case of normally distributed data. For non-normally distributed data, the Wilcoxon rank-sum test will be used for independent samples, and the Wilcoxon signed-rank test for dependent samples. For comparisons among multiple time points, the ANOVA (or Kruskal-Wallis test for non-parametric data) will be applied to independent samples, while repeated measures ANOVA (or Friedman test for non-parametric data) will be used for dependent samples. When appropriate, a *post hoc* test (e.g., Bonferroni correction or Tukey’s HSD) will be performed to adjust the *p*-value.

A p-value < 0.05 will be considered statistically significant.

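### For scale scores and biomarkers compared over three or more visits, repeated-measures ANOVA or Friedman drops every patient with one missing visit; a mixed model would keep the observed data

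*Protocol article*

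**What the plan says.** The Statistical analyses section assigns tests by type of comparison.

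- Primary responder endpoint: "The primary endpoint will be measured using the McNemar exact test".
- Two time points: "Differences in continuous variables (scale scores, biomarkers) will be tested using the unpaired and paired t-test", with Wilcoxon tests for non-normal data. The section stresses T0 against T1 and T2 against T3, which are two-visit comparisons.
- Several time points, same patients: "repeated measures ANOVA (or Friedman test for non-parametric data) will be used for dependent samples".

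On sample size, Participants states: "The study will enrol 20 CDD patients". It shows no allowance for loss.

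On loss, Study treatment says that patients who still cannot tolerate the product after an interruption "should be suspended from the study". Subject withdrawal adds "Patient parents/legal guardians may decide to terminate the study at any time" and lets the investigator end participation for adverse events or non-compliance.

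Table 1 gives the number of visits per outcome:

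- SDSC, GISI, MBAS, CDD-SA and CGI-I: T0, T2 and T4.
- Dried blood spots: T0, T1 and T3.
- Stool form, faeces, dietary survey and seizure diary: all five time points.
- PSI-SF: T0 and T4.

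**The concern.** Repeated-measures ANOVA in its standard form and the Friedman test both need a full row of visits per patient. A patient who misses one analysed visit leaves the test together with the values already recorded. This follows from a method that the article names, so an analysis plan that followed the sentence would inherit it.

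Two things are at stake. The first is precision, since a sample of 20 has little to spare. The second is bias. The listed reasons for leaving (intolerance, adverse events, non-compliance) may well go with poor response. In a single-arm trial no control group would show that the remaining patients are a favourable selection. The outcomes exposed are the scales and biomarkers measured at three or more visits, including the SDSC and GISI scores behind the secondary outcomes.

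**Working it through.** **The plan's own figure.** The article gives no dropout or missing-visit rate, so there is nothing to reproduce on this point. Its only power figure, 80%, belongs to the McNemar test and is not used here. All missingness rates, correlations and effects below are assumptions.

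**Step 1: patients lost to complete-row deletion.** With a fraction m missing independently at each of v visits, the share lost is 1 − (1 − m)^v, and the expected number of complete rows is 20 × (1 − m)^v.

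| m | Two visits (a pair) | Three visits | Five visits |
|---|---|---|---|
| 5% | 1 − 0.95² = 9.75% | 1 − 0.95³ = 14% (17.1 left) | 1 − 0.95⁵ = 23% (15.5 left) |
| 10% | 1 − 0.90² = 19% | 1 − 0.90³ = 27% (14.6 left) | 1 − 0.90⁵ = 41% (11.8 left) |

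At 3% missing per visit, 18.3 complete rows remain over three visits and 17.2 over five. At 20%, 10.2 and 6.6 remain.

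**Step 2: precision when visits are missing at random and intermittently.** Simulation with n = 20 and within-patient correlation 0.6. The entry is the variance of a two-visit contrast relative to a mixed model on all observed visits.

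| Analysis | 5% missing | 10% missing |
|---|---|---|
| Complete rows, three visits | about 1.1 | about 1.2 |
| Complete rows, five visits (T2-T3) | about 1.2 | about 1.6 |
| Planned paired test, T2-T3 | 1.04 | 1.09 |

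**Step 3: bias when poor early responders leave, SDSC/GISI schedule.** Visits T0, T2 and T4; n = 20. The four patients with the worst T0-T2 change leave after T2.

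| Contrast | Truth (SD units) | Complete rows | Mixed model |
|---|---|---|---|
| T0-T2 | −0.30 | −0.59 | −0.29 |
| T0-T4 | −0.50 | −0.65 | −0.50 |

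**Step 4: the same loss, but for T0-T1 in a five-visit outcome.** The four patients with the worst T0-T1 change leave after T1. The truth is −0.50. Complete rows give −0.79, the planned paired test −0.49 and the mixed model −0.49. The paired test is not biased here because those patients have both values.

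**Step 5: limits of the mixed model.** Three visits, n = 20, true T0-T4 change −0.50, correlation 0.5 / 0.7, unstructured covariance, about 25% to 29% of patients without T4 in the three dropout scenarios.

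| Loss mechanism | Complete rows | Mixed model |
|---|---|---|
| Depends on observed earlier response | mean −0.68 / −0.65 | mean −0.51 / −0.52 |
| Depends on the unseen T4 response | mean −0.85 / −0.79 | mean −0.76 / −0.72 |
| Random, patient leaves for good | SD 0.263 / 0.201 | SD 0.259 / 0.198 |
| Random, single visits missed | SD 0.252 / 0.195 | SD 0.234 / 0.180 |

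The bias goes in the first case and mostly stays in the second. Precision is hardly improved in the third case and largely restored in the fourth, where full data would give 0.222 / 0.168. In the first case the mixed-model estimate also varies more than the complete-row one (SD 0.29 against 0.26, and 0.22 against 0.20), which is the price of removing the bias.

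**The case against.** The strongest reply is that the plan does not assign its main comparisons to these tests. The primary endpoint uses McNemar. The stressed T0-T1 and T2-T3 contrasts fall to paired tests, which lose only incomplete pairs. A reader might infer that the estimated MF1 effect over T0-T1 is biased because later dropouts are deleted. The article does not support that: as Step 4 shows, the paired test keeps those patients and agrees with the mixed model. This part of the reply stands.

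A reader might also infer that a mixed model cures both bias and imprecision. Step 5 shows that it does not in general. Withdrawal, the mechanism that the article itself describes, is the pattern in which least precision is recovered. That stands too.

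A third reply is that the sleep and GI outcomes are defined by thresholds, that no rule for incomplete visits is stated, and that a condensed article may leave such handling to the full protocol or analysis plan. This stands in part. The article prescribes neither deletion nor which visits enter a multi-visit test, and missing detail is no fault here. But it does name the tests, says that they apply to scale scores and biomarkers, and those tests in standard form carry complete-row deletion with them. For SDSC and GISI, Table 1 has no T1 or T3 scores, so the stressed pairs cannot be formed as scheduled. A comparison of their three visits falls under the criticised sentence.

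**Conclusion.** The point holds for scale scores and biomarkers compared over three or more visits. There the named tests discard observed data and, if poor early responders leave, overstate improvement. In the SDSC/GISI-type scenario, a true T0-T2 change of −0.30 SD appeared as −0.59, and a T0-T4 change of −0.50 as −0.65.

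It does not reach the primary endpoint. For the T0-T1 and T2-T3 paired tests, the precision at stake is small (variance ratio 1.04 to 1.09 for T2-T3).

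The size in this trial cannot be fixed from the article, because no missing-data rate is given. The losses of 14% to 27% (three visits) and 23% to 41% (five visits) rest on an assumed 5% to 10% missing per visit, independent across visits. The bias figures rest on four of 20 patients leaving because of an observed poor response. The change is worth making because it is cheap and the sample is small, but it concerns secondary, other and biomarker outcomes only.

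**What to change.** Replace repeated-measures ANOVA/Friedman for dependent samples with a linear mixed model fitted by REML to all observed visits: visit as a categorical fixed effect, a patient random effect, a small-sample degrees-of-freedom correction such as Kenward-Roger, and a transform for skewed outcomes.

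Tie the contrasts to Table 1: for example T0-T2 and T0-T4 for SDSC and GISI, and T0-T1 and T2-T3 for five-visit measures.

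State that bias is removed only if missingness depends on observed data, and that little precision returns when patients leave for good. Add one sensitivity analysis for dropout related to unobserved response.

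The cost is a few sentences, slightly more analysis work and a model assumption to check. It needs standard software and no extra data.

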### Registration and guidelines

The study protocol reported here was written in compliance with the Standard Protocol Items, Recommendations for Interventional Trials (27).

The sponsor (no-profit) is Telethon Foundation, Seed grant CDKL5 Renewal 2023 caLL.

Kolfarma s.r.l. holds the license for the study supplements and is responsible for its supply. It has contributed to defining the eligibility criteria and treatment schedule for the study.

### Written informed consent

Participant parents or caregivers will receive an information sheet about the study along with an informed consent form for the collection of biological material. They will also be provided with a telephone number and an email address for any inquiries or to communicate their decision to withdraw from the study at any time.

### Patient confidentiality

To protect patient privacy, all CRFs, banked study samples, study drug accountability records, study reports, and communications will identify patients only by their assigned identification number. Patient confidentiality will be maintained and will not be publicly disclosed, except as permitted by applicable laws and regulations.

### Patient and public involvement

Patients and the public were not involved in developing the study protocol; however, the Associazione CDKL5 “Insieme Verso la Cura” supported subject enrollment and contributed to funding allocation.

## Discussion

CDD is a severe neurodevelopmental condition, characterized by early-onset seizures, intellectual disability, and motor impairments due to pathogenic variants in the *CDKL5* gene. The management of CDD is complex, particularly due to the associated treatment-resistant epilepsy and multiple co-occurring conditions.

Recently, the gut microbiota has emerged in influencing neurological outcomes (6, 20). CDD microbiota has been suggested to be enriched in specific bacterial taxa that seem to correlate with symptoms severity, such as *Lachnoclostridium* and *Enterobacteriaceae* with severe GI symptoms and *Peptostreptococcaceae, Coriobacteriaceae (Collinesella),* and *Erysipelotrichaceae* with daily epileptic seizures (16).

Emerging evidence suggests that modulation of the MGBA through approaches such as prebiotics, probiotics, postbiotics, and fecal microbiota transplantation (FMT) may play a promising role in the management of neurological disorders, including epilepsy^8.^

Thus, *ad hoc* medical foods and/or dietary modifications and/or probiotics may be considered as complementary treatment for CDD patients. These interventions may help restore gut microbiota balance, which has been linked to neurological health (28). The formulation MF2 has been investigated for a clinical trial study for the treatment of Rett syndrome (Trial registration number - ClinicalTrials.gov Identifier NCT05420805), a neurodevelopmental disorder that shares several clinical features with CDD (28). MF2 (ALAC/FOS/inulin/NaB) could offer a synergistic approach to managing CDD by improving gut health and reducing inflammation and may help to address both the gastrointestinal and neurological symptoms experienced by patients.

In conclusion, CDD is a debilitating and life-threatening neurodevelopmental disorder for which no therapies are available that address its core features. The study protocol presented here provides a potentially viable treatment for the core signs and symptoms of CDD, ranging from seizures to GI and sleep problems, and supports further trials in this population. The results of this study could pave the way for new therapeutic opportunities. Our aim is to significantly enhance the quality of life for patients and their caregivers, recognizing the pressing needs of individuals and families affected by this condition.
